## Abstract

**Background:**

Severe Acquired Brain Injury (sABI) presents significant challenges in clinical management and rehabilitation due to its diverse and complex nature. The primary objective of the Tiresia project is to identify medium and medium-to-long-term prognostic factors for patients with sABI and to develop outcome indicators to evaluate the quality of care in rehabilitation units.

**Methods:**

This paper outlines the protocol for a prospective observational multicenter study conducted within the Tiresia Network. The study relies on a comprehensive data collection with stringent quality control measures. Ethical considerations emphasize patient privacy protection and adherence to regulatory standards. All of the Italian intensive rehabilitation units dedicated to sABI patients were eligible to participate in the study. Twenty-seven of them joined the project and started the data collection.

**Discussion:**

The present study represents a comprehensive effort to address critical gaps in sABI research and practice through a multicenter, prospective study design. Through rigorous data collection, analysis, and ethical oversight, the Tiresia project endorses the commitment of the research community to advancing evidence-based care and optimizing patient outcomes in sABI rehabilitation.

**Clinical trial registration:**

The study was registered on ClinicalTrials.gov (ID: NCT04905264), on 24 May 2021.

## Introduction

1

Severe Acquired Brain Injury (sABI) is defined as a damage to the brain caused by an acute event. The origin can be traumatic and non-traumatic, such as vascular or hypoxic–ischemic. These events, which may result in temporary or permanent impairments, can profoundly affect motor, sensory, cognitive, emotional, and behavioral functions (1–3). The consequences of sABI are far-reaching, affecting not only the individuals directly impacted but also their families and broader social networks (4). The burden extends beyond the personal to include significant economic implications due to the costs associated with long-term care and rehabilitation (5, 6).

While the international literature offers insights into the global landscape of sABI (7, 8), unfortunately, there are no reliable statistics about its epidemiology in Italy. Nonetheless, extrapolations from data in other regions suggest that sABI is a major public health concern, with critical implications for the national healthcare system.

Effective management of sABI involves a continuum of care that spans from the acute phase, characterized by intensive resuscitative and neurosurgical interventions, to post-acute rehabilitation, aimed at optimizing functional recovery and quality of life (9). The complexity of sABI care is underscored by the diverse needs of patients across different phases of their recovery journey (10). Moreover, the absence of standardized approaches to rehabilitation and the heterogeneity in care delivery models across regions contribute to disparities in treatment outcomes and patient experiences (11).

Addressing the challenges inherent in sABI care requires a multifaceted approach that encompasses research, clinical practice, and policy initiatives. Central to this endeavor is the need to establish robust evidence regarding prognostic factors and quality of care in sABI rehabilitation. By elucidating the factors that influence patient outcomes and identifying best practices in care delivery, healthcare providers can optimize resource allocation, improve treatment efficacy, and enhance patient-centered care.

Tiresia, a network of Italian rehabilitation units dedicated to clinical research in rehabilitation medicine, represents a collaborative effort to advance knowledge and practice in sABI care (12). Through independent research projects and collaborative initiatives, Tiresia seeks to evaluate and improve the quality of care, promote evidence-based practices, and facilitate resource optimization in sABI rehabilitation.

This work presents the protocol of the first study of the Tiresia network, a prospective multicenter observational study aimed at establishing a robust framework to evaluate the quality of care in sABI units (13). Specifically, the study applies the well-established Donabedian’s model to evaluate the quality of healthcare based on outcome indicators (14).

## Methods and analysis

2

### Objectives

2.1

The overarching goal of the study is to establish a framework to evaluate the quality of care in sABI units based on outcome indicators. Using Donabedian’s model (14), an overall assessment of the quality of care of sABI units can be inferred from observed differences in patients’ outcomes after adjusting for differences, with respect to relevant prognostic factors, in the case-mix of the units. This project will therefore focus on the two key elements required in such a framework, i.e., the definition of the prognostic factors for sABI patients and the development of the outcome indicators to measure the quality of care.

Specifically, the primary objective of the Tiresia project is to identify medium and medium-to-long-term prognostic factors for sABI patients and evaluate their impact on rehabilitation outcomes. The study plans to identify key prognostic factors associated with each outcome measure at two different timings, 4 and 12 months after the injury.

The secondary objective of the study is to develop indicators of the quality of care provided by the participating rehabilitation units. In particular, the quality-of-care indicators will be based on the patients’ outcomes and span the multidimensional nature of the recovery assessment.

To formalize the research question using a standardized approach, we applied the Population, Intervention, Comparison, Outcome (PICO) framework (15). Specifically, the target population (P) includes all patients admitted to sABI units. The exposure of interest (or intervention, I) is the admission to each specific sABI unit, as the goal of the study is to compare the quality of care of each center to the average care, and there is no comparison (C). The primary outcomes (O), described in detail in Section 2.2, are impairments in body functions that are critical for functional independence.

### Outcomes

2.2

Unlike traditional prognostic assessments, which often focus on mortality, this study primarily investigates the likelihood of functional recovery following the acute event. In particular, the study adopts a multidimensional assessment of the recovery.

The primary outcomes of the study are three functional outcomes related to critical events in the rehabilitation pathway: successful removal of the tracheostomy cannula, achievement of trunk control, and complete oral feeding resumption. Using the International Classification of Functioning, Disability and Health (ICF) to characterize impairments through an international standard for functioning and disability (16), the three outcomes are related to impairments in body functions and, specifically, to respiration functions (code b440), the tone of the muscles of the trunk (code b7355) and digestive functions (code b515). These outcomes are relevant to characterize the recovery of patients because they are critical markers of functional independence, as success in each of these tasks results in a drastic reduction in the patient’s need for assistance.

Three standardized and validated scales to investigate cognitive impairment, disability and autonomy are the secondary outcomes of the study: the Oxford Cognitive Screen (OCS) (17), the Glasgow Outcome Scale – Extended (GOS-E) (18) and the Supervision Rating Scale (SRS) (19), respectively.

Notably, all of the identified outcome measures are strategic to evaluate the quality of the provided care because they require the capacity to effectively organize the work of a broad interdisciplinary staff, including physicians, nurses, physiotherapists, psychologists, speech and language therapists, and occupational therapists.

### Study design

2.3

The study adopts an observational, multicenter, prospective design. The multicenter nature of the study, which is facilitated by the existing Tiresia network, allows for the recruitment of a diverse patient population, enhancing the generalizability of study findings and facilitating collaborative research efforts.

### Participating centers and study population

2.4

All Italian intensive rehabilitation units dedicated to sABI patients are eligible and invited to participate in the study. This inclusive approach ensures representation from heterogeneous clinical settings and geographic regions, enriching the study’s external validity and enabling the exploration of regional variations in care delivery and outcomes. A total of 27 centers participated in the study.

All adult patients with sABI consecutively admitted to the participating units during the study period are eligible for the study. Patients admitted later than 14 weeks after the acute event are excluded as, for these patients, evaluating the prognostic role of risk factors at the admission to the rehabilitation unit and the achievement of the outcomes of interest within the stay in the unit would be pointless, due to the closeness of the potential study enrollment and the first timing of outcome evaluation (i.e., 4 months).

### Recruitment

2.5

The study duration spans 4 years, encompassing patients’ enrollment, follow-up assessments, and data analysis. We planned to enroll new patients in the study for 30 months. An additional 12-month period will be necessary to collect data on the 12-month follow-up for the last patients enrolled in the study.

### Data collection

2.6

Central to the study design is the comprehensive collection of patient characteristics and rehabilitation outcomes, facilitated through the development of an ad-hoc electronic Case Report Form (eCRF), which serves as the primary tool to ensure the uniformity and accuracy of data across participating centers. The data collection is organized in three forms corresponding to different timepoints: sABI admission, 4-month and 12-month assessments. The first form describes the conditions of the patient at admission to the sABI unit and includes demographics, socioeconomic factors (e.g., working status, education level, caregiver support), comorbidities, characteristics of the acute event (e.g., timing, etiology), interventions and procedures received in the acute phase (e.g., intubation, tracheostomy), procedures undergoing at sABI unit admission (e.g., mechanical ventilation, O_2_ therapy), colonizations and infections by Multi-Drug Resistant Organisms (MDRO), parameters describing the conditions at sABI unit admission (e.g., heart rate, respiratory rate) and scores (e.g., Level of Cognitive Functioning – LCF, Early Rehabilitation Barthel Index – ERBI, Disability Rating Scale – DRS). At the 4- and 12-month follow-up assessments, the staff of the participating centers is required to evaluate the outcome measures of interest for the study, either through an on-site visit or a telephonic/video conferencing interview. Furthermore, upon registration for the study, sABI units are required to fill out a form describing their structural and organizational characteristics.

To ensure data quality and integrity, the study implements robust quality control measures at multiple levels. Each severe sABI Rehabilitation Unit designates an experienced clinician responsible for protocol adherence and data integrity at the local level. The Coordination Center holds regular meetings with representatives from the participating centers to address any challenge with the study, provide guidance, and ensure consistency and standardization in the collected data across all units. An indexed operating manual describing the data collection items has been developed and is accessible through a simple click during data entry. In addition, the detailed definition of the variables to be collected is clearly displayed on the screen, to avoid misinterpretation of the required fields. A real-time set of controls operates during data collection and includes completeness checks, warnings and errors to promptly highlight discrepancies in the inputted information. The rules for defining warnings and errors will be continuously revised and implemented based on user suggestions. They will be of five types: validity, plausibility, logical congruence, clinical congruence, and definition congruence. Furthermore, data will be centrally processed for epidemiological inconsistencies that cannot be automatically detected during data entry.

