### Statistical analysis

2.7

The statistical analysis of study data is conducted by the Tiresia Coordination Center at the Istituto di Ricerche Farmacologiche Mario Negri IRCCS. Analyses will employ various analytical techniques to address the study objectives and research questions. Descriptive statistics, including proportions, medians and interquartile ranges, and means and standard deviations, will be used to summarize and present the collected data.

The primary analysis focuses on identifying prognostic factors predictive of the identified outcome measures and in particular: the achievement of the three objectives in the rehabilitation process (i.e., successful decannulation, trunk control and complete oral feeding); a pathological result in the five cognitive domains investigated by the OCS (attention, language, numerical cognition, praxis and memory) (20); the value of the GOS-E scale, simplified into 4 levels (death or vegetative state, severe disability, moderate disability, good recovery); the value of the SRS scale, simplified into five levels (independent, night supervision, part-time supervision, indirect full-time supervision, direct full-time supervision). Separate regression models will be developed for each outcome and timing (4 and 12 months from the acute event). Logistic regression models will be used to assess the achievement of the rehabilitation objectives and the abnormalities in the OCS cognitive domains, which are dichotomous variables. Multinomial logistic regression models will be used to handle the GOS-E and SRS scales, which are categorical variables with four and five levels, respectively. To account for the large number of candidate predictors to screen as potential prognostic factors, we will use the technique of Least Absolute Shrinkage and Selection Operator (LASSO) (21), which is a popular approach to perform variable selection when the number of potential predictors is large compared with the sample size (22).

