The secondary analysis of the study is aimed at developing quality of care indicators for sABI Units. This step will leverage the prognostic models developed for the main analysis, which will be employed to calculate the expected number of failures for each dichotomous outcome and the expected value of each of the possible levels for the categorical variables. Because the models will be developed using all patients admitted to all participating centers, they represent the average behavior and can be used as a reference (or benchmark) for quality-of-care assessment. The comparison in each sABI Unit between the expected and observed frequencies of the outcomes will constitute the indicator of quality of care for the department. The most common approach to perform this comparison is the standardized event ratio (SER), i.e., the ratio of observed and expected events (23). A SER value less than 1 indicates a lower-than-average number of events, while a value greater than 1 indicates that a center experienced more events than expected. Each SER will be provided with the corresponding confidence interval. Importantly, SER heavily relies on the prognostic model used as a benchmark of quality of care. In order to assess the robustness of the results against the prognostic model developed, indicators based on nonparametric methods, independent of that model, will also be used. In particular, a matching-based design will be applied (24). For each center, each patient will be matched to *K* other patients admitted to different units but similar to the selected patient with respect to the identified prognostic factors. Matching will be performed using state-of-the-art algorithms, including optimal and cardinality matching. This strategy will create a control group for each center with a similar case mix with respect to the relevant prognostic factors. The quality of care will be measured in terms of risk difference for each failure indicator, provided with the appropriate confidence interval. The parameter *K*, which sets how many control subjects will be matched to each patient, will be chosen based on the size of the database. We expect to be able to perform this analysis with a value of *K* between 1 and 3.

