## Conclusion

5

The present study, promoted by the Tiresia network, represents a comprehensive effort to address critical gaps in sABI research and practice through a multicenter, prospective study design. Specifically, the overarching goal of the study is to assess the quality of care in sABI units using outcome indicators while accounting for differences in patient case-mix based on prognostic factors measured at admission. Notably, the study is not focused on the assessment of the effectiveness of specific treatments, interventions or policies. Determining treatments associated to the best outcomes is a medium-to-long term goal of the Tiresia network, which can be achieved by performing audits and further investigations in the centers showing a quality of care significantly deviating from the average. This study will therefore offer the possibility to generate hypotheses on the effectiveness of methods of care, which will be tested with further studies, possibly extending the data collection and leveraging the formed network of sABI units.

A distinctive and innovative feature of the study is the unprecedented number of participating centers (27 sABI units), whose involvement has been facilitated by the Tiresia network. The study aims at establishing one of the largest data collections in the field in Italy and internationally in terms of patient enrollment. Such a broad participation provides a robust platform for collecting diverse and comprehensive data, enhancing the generalizability and relevance of study findings.

Another strength of the study lies in its robust underlying methodology, which is evident in several aspects of the study design. These include the standardized definition of primary outcome measures using the ICF framework, the implementation of stringent data quality control procedures to ensure consistency in data collection across sites, and the application of advanced statistical methods to identify deviations from the average quality of care among the centers.

This research endeavor will be a unique opportunity to advance knowledge and improve outcomes for sABI patients across Italy and beyond by elucidating prognostic factors and developing quality-of-care indicators. Through rigorous data collection, analysis, and ethical oversight, the Tiresia project endorses the commitment of the research community to advancing evidence-based care and optimizing patient outcomes in sABI rehabilitation.

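### Any outcome may be assessed on site or remotely, and neither unit indicator accounts for mode, so trunk-control and OCS comparisons between units can be distorted where units differ in remote follow-up

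*Protocol article*

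**What the plan says.** Section 2.6 (Data collection) states that at the two follow-up times "the staff of the participating centers is required to evaluate the outcome measures of interest for the study", and that this is done "either through an on-site visit or a telephonic/video conferencing interview". The sentence covers all outcomes and both times. It gives no rule for choosing between modes and excludes no outcome from remote assessment.

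The primary outcomes in Section 2.2 are "successful removal of the tracheostomy cannula, achievement of trunk control, and complete oral feeding resumption". The OCS is a secondary outcome, analysed in Section 2.7 as "a pathological result in the five cognitive domains investigated by the OCS"; praxis is one of the five.

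For the unit comparison, Section 2.7 uses the prognostic models to "calculate the expected number of failures for each dichotomous outcome" and then says: "The most common approach to perform this comparison is the standardized event ratio (SER), i.e., the ratio of observed and expected events". Section 5 describes the adjustment as "accounting for differences in patient case-mix based on prognostic factors measured at admission". The nonparametric check in Section 2.7 matches each patient to patients of other units on the same prognostic factors.

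Section 2.6 also describes safeguards: an operating manual, on-screen definitions, automated checks and regular meetings. None is said to deal with the mode of assessment.

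**The concern.** The outcomes differ in how well they tolerate remote assessment. Whether a cannula is in place, or whether a patient eats fully by mouth, is a fact that can be told to an interviewer. Trunk control is a physical finding, which Section 2.2 ties to trunk muscle tone. It can be examined on site and perhaps watched on video, but over a voice call it can only be reported. The OCS domains are results of tasks that the patient performs, and a task such as praxis is hard to score without seeing it.

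Mode is decided after admission, so it cannot be among the admission factors behind the expected counts. The pooled benchmark therefore mixes whatever modes the network used, while a unit's observed count reflects its own mix. Matching on the same admission factors does not remove this, so the robustness check shares the weakness.

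The secondary objective is at stake. Section 5 intends units that deviate significantly from the average to be audited and studied further. A deviation produced by the way outcomes were collected would misdirect that work. The primary objective is touched less directly: an admission factor such as caregiver support could pick up some of the mode effect if it also predicts remote follow-up.

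**Working it through.** **Inputs from the document.** Section 2.8 gives 60 admissions per unit per year, 15 units, 30 months of enrolment and a failure rate of 10%. These reproduce the plan's own figure: 15 × 60 × 2.5 = 2,250 patients, and 0.10 × 2,250 / 10 = 22.5, stated as 22 predictors. One unit contributes 60 × 2.5 = 150 patients and about 15 expected failures. The plan gives no figure for mode of assessment.

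**Assumed inputs.** The error of remote relative to on-site assessment is not in the document. The range taken is that remote assessment misses 10 to 30% of true failures, or wrongly records failure in 2 to 5% of non-failures.

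**Formulas.** Let p be the true failure rate, Se the share of failures detected remotely and Sp the share of non-failures correctly classified remotely. The recorded rate in an all-remote unit is q = p·Se + (1 − p)(1 − Sp). Care and case mix are taken as identical. If a share w of network assessments is remote, the benchmark is b = (1 − w)p + wq. The SERs are q/b (remote unit) and p/b (on-site unit), so their ratio is q/p whatever w is.

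**Results at p = 0.10**

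| Remote error | q | SER ratio q/p | SERs if w = 0.5 (remote / on-site) |
|---|---|---|---|
| 10% of failures missed | 0.090 | 0.90 | 0.95 / 1.05 |
| 20% missed | 0.080 | 0.80 | 0.89 / 1.11 |
| 30% missed | 0.070 | 0.70 | 0.82 / 1.18 |
| 2% false failures | 0.118 | 1.18 | 1.08 / 0.92 |
| 5% false failures | 0.145 | 1.45 | 1.18 / 0.82 |

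The first three ratios do not depend on p. The last two do: at p = 0.30 they are 0.314/0.30 = 1.05 and 0.335/0.30 = 1.12.

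**Mixed use.** Take half the patients in units with 60% remote follow-up and half in units with 30%, with 20% of failures missed remotely. The detected fractions are 1 − 0.6 × 0.2 = 0.88 and 1 − 0.3 × 0.2 = 0.94, with mean 0.91. The SERs are 0.88/0.91 = 0.97 and 0.94/0.91 = 1.03.

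**Against chance.** With 15 expected failures the standard error of an SER near 1 is about 1/√15 = 0.26. Assume an exact Poisson 95% interval and a fully on-site benchmark. A 150-patient all-remote unit would then have an interval excluding 1 in about 4% of cases (10% missed), 17% (30% missed) or 33% (5% false failures), against about 3% for an on-site unit.

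**The case against.** The text permits two channels. It does not report how often each is used, or that use differs between units. If the mix is similar everywhere, the effect largely cancels in observed over expected. An article may leave item-level rules to the operating manual, which is not shown. Remote contact includes video, on which trunk control and perhaps some OCS tasks could be watched. All-or-none use of one mode by a unit is extreme, and at realistic mixes the shift may be well inside chance variation.

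All of this stands, and it limits the point to a possible bias of unknown size. It does not remove it. The article states a measurement rule rather than leaving one out, that rule allows either mode for all outcomes, and the safeguards it lists do not mention mode.

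Some stronger readings are tempting but not supported:

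- A reader might infer that units do measure these outcomes differently. The document shows only that they may.
- A reader might infer that every telephone follow-up loses the OCS praxis result. The document does not describe how the OCS is administered.
- A reader might infer that discharge setting or later recovery would emerge as false prognostic factors. Candidate predictors are measured at admission, so at most admission proxies could carry the effect.
- A reader might infer that change from 4 to 12 months is confounded with change of mode. Section 2.7 fits separate models for each time and plans no such contrast.
- A reader might infer that remote units would look better. False failures reverse the direction.

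**Conclusion.** The point holds as a weakness in a stated measurement rule: mode may vary by outcome, patient and unit, and neither the SER nor the matching check accounts for it. For trunk control, a primary outcome, and for the OCS domains, a difference between units in remote follow-up would pass unadjusted into the quality indicators. The possible effect runs from negligible (SERs of 0.97 and 1.03 under mixed use) to an SER ratio of 0.70 or 1.45 between an all-remote and an all-on-site unit. These figures rest on assumed error rates, on identical care and case mix and, for the 1.18 and 1.45 ratios, on the 10% failure rate. Neither size nor sign can be read from the document. The change is worth making because it is cheap and the plan has no other means of detecting the problem. No sample-size figure changes.

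**What to change.** 1. Record the mode (on site, video, telephone) for each outcome at each follow-up in the eCRF, retrospectively where it can be recovered.
2. Do not score OCS domains or trunk control from a voice-only contact as if the patient had been examined. Flag them as reported (trunk control) or missing (OCS).
3. Keep direct observation of trunk control wherever the patient is seen. Replacing it with a common question set for everyone would remove the observed finding against which reports could be checked.
4. Report the share of each mode by unit alongside the indicators.
5. Pre-specify a sensitivity analysis of the trunk-control and OCS SERs restricted to directly observed assessments. Weight it by the inverse probability of direct observation given admission data and, for the 12-month outcomes, 4-month data. The weights are needed because patients who are seen are a selected group.

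Cost: one eCRF field per outcome, an addition to the operating manual and one extra analysis, with no additional visits. Some trunk-control and OCS results, mainly at 12 months, will become missing or drop out of the sensitivity analysis. Units have already started collecting data, so mode may not be recoverable for assessments already done.
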